### Measurements

To comprehensively evaluate the effects of the 12-week exercise intervention, the measurements in this study are systematically categorized into primary outcomes, secondary outcomes, exploratory outcomes, and control and monitoring variables. The core construct of our investigation is esports performance, which we conceptualize as a multidimensional framework comprising both objective operational skills and esports-related psychological skills. To implement our multidimensional evaluation of esports performance while maintaining strict statistical rigor, the primary outcome is specifically defined as flicking capacity in esports performance (quantified by the total number of targets successfully hit during a 1-minute task). This metric was strategically selected as the primary endpoint because it effectively captures “aiming throughput”, inherently accounting for the speed-accuracy trade-off by rewarding both speed and precision.

The secondary outcomes encompass the remaining dimensions of our esports performance framework, including other operational metrics (detection capacity, tracking performance, overall shooting accuracy, and reaction speed) and esports-related psychological skills, as well as body composition and physical competence.

Other outcomes were strategically selected to support and enhance the validity of our primary analysis while maintaining a clear focus on the main research objectives. These measures serve three specific purposes: (1) to identify and control for potential confounding variables through covariate analyses, ensuring robust assessment of the exercise’s effect on esports performance; (2) to monitor and standardize key lifestyle factors (e.g., sleep, affect, physical activity, and dietary intake) known to influence cognitive and gaming performance, thereby isolating the intervention effect; and (3) to enable supplementary analyses exploring potential mechanisms underlying the relationship between physical exercise and esports performance.

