#### Physical activity and sitting time.

The evaluation of both physical activity and sitting time will be conducted through the bilingual (English-Chinese) version of the self-administered International Physical Activity Questionnaire (IPAQ) long form. This is a widely used instrument, and its Chinese translation has well-established reliability and validity among Chinese cohorts [87,88]. This specific version of the IPAQ comprises a set of 27 questions designed to ascertain the duration (in minutes) of participants’ involvement in physical activities of different intensity levels.

Moreover, to prevent the inclusion of participants who already had a regular habit of engaging in aerobic exercise, spontaneously engaging in additional aerobic exercise during the 12-week intervention period that could potentially influence the final test results, we excluded players who already had a regular habit of engaging in cardiovascular exercise during the recruitment process.

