### Intervention

From previous literature, it has been observed that a HIIT protocol involving 10 × 1-minute bouts at 80–90% of maximum heart rate (HRmax) with 1-minute recovery periods at 40–50% of HRmax is deemed effective [92–94]. Moreover, this intensity and interval have shown significant short-term effects on esports performance in previous studies [27]. This study will follow this protocol for the HIIT exercise group. MICT in this study will consist of continuous exercise at 64–76% of HRmax for 20 minutes, ensuring that the total exercise duration is equivalent to the HIIT protocol to maintain comparable training volumes between groups. A standardized 3-minute warm-up with dynamic stretching and a 3-minute cool-down at 50% HRmax will be added at the beginning and end of each exercise session for both intervention groups. Participants in both intervention groups will be required to complete their respective exercise protocols three times per week throughout the 12-week intervention period. Real-time heart rate monitors (Polar Pacer) will be used to ensure intensity during exercise sessions. In addition, a rating of perceived exertion (RPE) will be employed in each training session utilizing the 6–20 Borg scale [95]. During high-intensity intervals, participants will be instructed to maintain an RPE between 15–18, while during the low-intensity intervals, warm-up, and cool-down phases, an RPE of 11–13 will be targeted [96]. For the MICT group, participants will maintain a moderate-intensity effort corresponding to an RPE of 12–14 throughout the continuous exercise session. Meanwhile, all training sessions will be guided by a professional fitness trainer who will ensure the professionalism and safety of the entire exercise process.

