### Data analysis

An intention-to-treat (ITT) analysis will be conducted as our primary analytical approach to evaluate the overall effectiveness of the intervention. Additionally, a per-protocol analysis will be performed as a sensitivity analysis, which will only include participants who met the predefined adherence criteria. Missing data will be addressed using the Multiple Imputation by Chained Equations (MICE) technique. The normality of the data will be assessed using the Shapiro-Wilk test, and Levene’s Test will be used to assess the homogeneity of variances. Continuous variables will be presented as means with standard deviations (SD) or medians with interquartile ranges (IQR), depending on their data distribution. Categorical variables will be presented as frequencies and percentages. Baseline characteristics among the three groups will be compared using a One-way Analysis of Variance (ANOVA) for normally distributed continuous variables, a Kruskal-Wallis H test for non-normally distributed continuous variables, and Chi-square tests for categorical variables.

To test the main hypothesis, the primary outcome is defined as flicking capacity. Generalized Estimating Equations (GEEs) will be used to determine the group-by-time interaction effect for both the primary and secondary longitudinal outcomes. To rigorously specify the GEE models, the distributional family and link function will be selected based on the specific nature of each outcome variable. An exchangeable working correlation structure will be specified to account for the within-subject correlation of repeated measures across time points. Furthermore, robust standard errors (the sandwich estimator) will be utilized to ensure valid statistical inference even if the working correlation structure is misspecified.

Furthermore, changes in monitored lifestyle variables (i.e., dietary intake, physical activity, and sleep quality) over the intervention period will be evaluated. If any of these variables exhibit significant changes or between-group imbalances, they will be incorporated as covariates in the GEE models to adjust for potential confounding effects, thereby isolating the true effect of the exercise interventions.

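### The covariate rule can put post-randomisation physical activity, diet and sleep into the primary GEE, which can shift its estimate away from the effect of assignment

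*Protocol article*

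**What the plan says.** All references are to the protocol article.

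- **Primary analysis (Data analysis).** "An intention-to-treat (ITT) analysis will be conducted as our primary analytical approach to evaluate the overall effectiveness of the intervention". GEEs "will be used to determine the group-by-time interaction effect for both the primary and secondary longitudinal outcomes".
- **The rule (Data analysis).** The section states that "changes in monitored lifestyle variables (i.e., dietary intake, physical activity, and sleep quality) over the intervention period will be evaluated". It continues: "If any of these variables exhibit significant changes or between-group imbalances, they will be incorporated as covariates in the GEE models". The stated purpose is "to adjust for potential confounding effects, thereby isolating the true effect of the exercise interventions".
- **Rationale (Measurements).** The supporting measures are collected, among other purposes, "to identify and control for potential confounding variables through covariate analyses".
- **Activity measure (Physical activity and sitting time).** The article names its instrument in these words: "The evaluation of both physical activity and sitting time will be conducted through the bilingual (English-Chinese) version of the self-administered International Physical Activity Questionnaire". It is the long form, which records minutes at different intensities.
- **Treatment contrast.** Both exercise arms must "complete their respective exercise protocols three times per week throughout the 12-week intervention period" (Intervention). Controls receive nothing (Experimental design). Everyone enters with fewer than two structured sessions a week (Participants).

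The article does not limit the rule to baseline values, does not exclude trial sessions from the questionnaire, and does not keep a model without these covariates as primary.

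**The concern.** Randomisation makes the arms comparable at baseline. A difference in activity, diet or sleep that appears during the 12 weeks is an effect of allocation or a chance difference. It is not a confounder of the allocation effect, so adjusting for it does not isolate that effect. It changes the question from what assignment to exercise does to what assignment does with the adjusted variable held constant. It can also introduce bias from any common cause of that variable and gaming performance.

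The three variables differ. Measured physical activity may contain the prescribed training, so the covariate may partly be the treatment, and the rule becomes more likely to fire the better participants comply. Diet and sleep are possible mediators only, and participants are asked to keep both as usual.

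There is a second, smaller problem. Covariates are chosen by significance tests on in-trial data, so the primary model is not fixed before the data are seen.

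At stake is the primary estimate: a real benefit that works partly through being more active could be reported as smaller or absent.

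**Working it through.** The plan gives no figure for how often the rule fires or what it does to the estimate, so there is none to reproduce. Both are worked out below as ranges.

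**Inputs from the article.** Three sessions a week. Session length 20 min (HIIT 10 × (1 + 1) min, MICT 20 min continuous), plus 3 min warm-up and 3 min cool-down. d = 0.4. 52 per arm after 20% dropout, 65 recruited. Two-sided α = 0.05.

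**Assumptions not in the article.** The SD of weekly activity minutes, the rise in measured activity, the share of the effect that runs through activity, and the reliability of the questionnaire.

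**Step 1: prescribed contrast.** 3 × 20 = 60 min/week, or 3 × (20 + 3 + 3) = 78 min/week, against none in the control arm.

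**Step 2: how often activity triggers the rule.** For one exercise arm against control, power ≈ Φ(78 / (SD × √(2/52)) − 1.96). The within-arm column is a paired t-test of a 78 min change with n = 52, reading the SD as the SD of change.

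| Assumed SD (min/week) | 78 / (SD × √(2/52)) | Between-arm trigger | Within-arm trigger |
|---|---|---|---|
| 80 | 4.97 | >99% | 100% |
| 120 | 3.31 | 91% | >99% |
| 160 | 2.49 | 70% | 93% |
| 240 | 1.66 | 38% | 63% |
| 300 | 1.33 | 26% | 45% |

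These figures suppose that the questionnaire captures the trial sessions and that other activity does not change.

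**Step 3: what adjustment does, by algebra.** Let the total effect be 0.4, the mediated share m and the rise in activity Δ. The direct part is 0.4(1 − m) and the activity coefficient is γ = 0.4m/Δ. Unadjusted, the model estimates 0.4(1 − m) + γΔ = 0.4. With well-measured activity held constant at each visit, it estimates 0.4(1 − m): 0.2 at m = 0.5 and 0 at m = 1, whatever Δ is.

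**Step 4: check by simulation of the planned design.** Three arms of 65, three visits, complete data, linear GEE with exchangeable correlation and robust standard errors. Residual outcome SD 1, within-person correlation 0.5, exercise effect 0.4 at week 12 and 0.2 at week 16, Δ = 1 SD, 300 runs. The entries are the week-12 HIIT-versus-control interaction, with power in brackets. Monte Carlo error of the estimates is about 0.18/√300 ≈ 0.01.

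| Form in which activity enters | Full mediation | Half mediation |
|---|---|---|
| Not included | 0.395 (56%) | 0.376 (61%) |
| Time-varying value | −0.011 (5%) | 0.175 (16%) |
| Change score with time interactions | −0.014 (6%) | 0.175 (14%) |
| Baseline value only | 0.395 (56%) | 0.376 (61%) |
| Change score, main effect only | 0.395 (56%) | 0.376 (61%) |

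With Δ = 0.5 SD the time-varying form gave −0.007 (full) and 0.200 (half).

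The last two rows are unchanged because, with complete data, the interaction is a contrast of within-person changes. A covariate that is constant over time cannot move it.

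**Step 5: measurement error.** Under full mediation with time-varying entry, an assumed reliability of 0.5 leaves about 0.25 of the 0.4, and a reliability of 0.3 leaves about 0.33. A noisy questionnaire removes less of the effect.

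**The case against.** The strongest reply is that the rule targets spontaneous extra exercise. The section on physical activity names that worry, and trial sessions are logged separately through the Polar system. That may be the intent, but the article does not say it, and the questionnaire as described does not separate the two. Activity outside the trial is also post-randomisation and may respond to allocation.

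The remaining objections limit the claim, and they stand:

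- **Form of entry.** The article does not fix it. A single change score entered as a main effect would leave the tested interaction unchanged in a complete-data linear GEE. For sleep and diet the text describes assessment only around the pre- and post-intervention tests, so time-varying entry at all three visits is not clearly available for them.
- **Baseline imbalance.** If imbalance meant baseline imbalance only, that part of the rule would not bias the effect, though it would still be data-driven.
- **Certainty of firing.** A reader might infer that the rule is bound to fire because the questionnaire counts the training. The article is silent on whether it does, and the trigger probability depends on an unknown SD.
- **Loss of the whole effect.** A reader might infer that the benefit would vanish. That needs full mediation, a well-measured covariate and a particular form of entry, none of which the article supports.
- **Conflict with ITT.** A reader might call this a flat contradiction. Analysing everyone as randomised is compatible with covariates. What may change is the quantity estimated.

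**Conclusion.** The concern holds in a conditional form. As written, the rule is mandatory, it covers the primary model, and it acts on variables that allocation can change. Following it can move the primary estimate from the effect of assignment to an effect with activity held constant.

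The size cannot be fixed from the article. The between-arm trigger for activity alone runs from about 26% to over 99% for assumed SDs of 300 down to 80 min/week. Once triggered, a true effect of 0.4 SD falls to about 0.2 (half mediation) or about 0 (full mediation) if well-measured activity enters as a time-varying value or with a time interaction. The loss is smaller with an unreliable questionnaire, and there is none with a time-constant main effect and complete data. The bias is therefore possible and potentially large, but not certain. The data-dependence of the primary model follows from the rule whichever form is used.

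**What to change.** 1. Remove the conditional rule from the primary ITT GEE.
2. Prespecify pre-randomisation covariates only: the gaming-experience stratum and, if wanted, baseline IPAQ or PSQI.
3. Keep baseline flicking capacity as a repeated outcome in the GEE. Make it a covariate only if the baseline row is dropped from the outcome; it should not serve as both.
4. Report post-baseline activity, diet and sleep by arm. Use them only in labelled sensitivity or exploratory mediation analyses, with the form of entry stated and with trial sessions (from the Polar records) separated from other activity.
5. Align the confounding rationale in the Measurements section with this.

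The cost is about one paragraph of wording. No change to data collection or sample size is needed.

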**Methods:**

In this three-arm randomized controlled trial, 195 FPS gamers (aged 18–29) will be randomly assigned to HIIT, MICT, or control groups. Interventions consist of three weekly sessions for 12 weeks (HIIT: 10 × 1-minute high-intensity bouts interspersed with 1-minute active recovery; MICT: 20-minute continuous moderate-intensity exercise). The primary outcome is flicking capacity (a core metric of esports performance). Secondary outcomes include other gaming operational metrics, esports-related psychological skills, body composition, and physical competence. All outcomes will be assessed at baseline, post-intervention (12 weeks), and follow-up (16 weeks).

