Choosing to use a third-party shooting program for testing instead of a specific game's custom approach has several advantages. Firstly, it ensures that all shooting game players have the same level of familiarity with the testing program, preventing individual players from obtaining higher esports performance scores due to their proficiency in a chosen game. Secondly, Aim Lab is primarily a training program focused on practice rather than entertainment, and it is unlikely that casual players would engage in regular training with this program. By selecting this software, we can avoid the potential influence of players’ habitual use of Aim Lab during the 12-week intervention, which could enhance their proficiency and subsequently affect the final performance test. Additionally, we excluded habitual users of Aim Lab during the screening phase to mitigate this issue. On the other hand, using a specific mainstream shooting game for testing would make it difficult to control the spontaneous participation of players who are loyal users of those games during the 12-week intervention, leading to an increase in proficiency and potentially affecting the final game performance test. Furthermore, Aim Lab, being a dedicated shooting training and testing software, provides detailed test scores for different dimensions of shooting, such as reaction time and accuracy. Compared to previous studies that used custom modes within specific esports games for testing, using Aim Lab offers a more objective approach, avoiding subjective factors or errors dependent on assessors [27].

Before the Aim Lab test begins, each participant will undergo a warm-up session to familiarize themselves with the software, mouse, and keyboard setups. Razer Synapse will be used to help participants set the DPI (Dots per inch). All Aim Lab tests will be conducted on the same computer in our laboratory, using identical mouse and keyboard setups.

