The primary outcome will be tested at a two-sided α level of 0.05. For the secondary outcomes, the resulting *p*-values for the group-by-time interaction effects derived from the GEE models will be adjusted using the Benjamini-Hochberg False Discovery Rate (FDR) method. If significant main or interaction effects are detected in the GEE model, simple effect analyses and post-hoc pairwise comparisons will be performed within the GEE framework using estimated marginal means with a Bonferroni adjustment.

Prior to investigating potential associations, we will first test for true inter-individual differences in response to the intervention by comparing the variance of the change between the groups [99]. If true inter-individual variability is confirmed, Pearson’s or Spearman’s rank correlation coefficients will be utilized, as appropriate, to investigate potential associations between esports performance indicators and hand correlates, body composition, and physical competence. To account for multiple testing in these correlation analyses, p-values will be adjusted using the Benjamini-Hochberg FDR method.

All statistical analyses will be conducted using R software (version 4.4.2). A two-sided *p*-value of < 0.05 will be considered statistically significant. To indicate the precision of the estimates, 95% confidence intervals (CIs) will also be calculated and reported.

For the exploratory qualitative component, all semi-structured interviews will be audio-recorded and transcribed verbatim. The transcripts will be analyzed using thematic analysis, facilitated by NVivo 12 software, to identify, analyze, and report recurring themes within the participants’ subjective experiences. Although the sample size is fixed by the intervention design, we will continuously monitor for thematic saturation during this data analysis phase. Rather than formally merging these findings with the quantitative data in a mixed-methods matrix, the qualitative themes will be utilized during the interpretation phase to contextualize the objective performance outcomes. This approach will provide a deeper understanding of the participants’ perspectives and assist in elucidating the potential underlying mechanisms between aerobic exercise and esports performance.

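### Any significant main effect, not only the group-by-time interaction, opens the post-hoc arm comparisons, and the primary test is not tied to week 12

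*Protocol article*

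**What the plan says.** All of the analysis text is in the Data analysis section of the protocol article.

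- **Test of the main hypothesis.** "Generalized Estimating Equations (GEEs) will be used to determine the group-by-time interaction effect for both the primary and secondary longitudinal outcomes".
- **Level.** "The primary outcome will be tested at a two-sided α level of 0.05". For secondary outcomes, only the interaction p-values enter the Benjamini-Hochberg FDR adjustment.
- **Rule for follow-up tests.** "If significant main or interaction effects are detected in the GEE model, simple effect analyses and post-hoc pairwise comparisons will be performed" and these are run "within the GEE framework using estimated marginal means with a Bonferroni adjustment". The set of comparisons that the Bonferroni factor covers is not given.
- **Primary outcome.** Under Measurements, "the primary outcome is specifically defined as flicking capacity in esports performance", counted as hits in one minute. No visit is attached to it there, in the Abstract or in Data analysis.
- **Visits and aims.** Outcomes are taken at baseline, week 12 and week 16. The Abstract's objectives separate the effect of the 12-week programmes (objective 1) from its persistence four weeks later (objective 2).

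**The concern.** With three arms and baseline in the outcome vector, only the interaction carries the randomised comparison. The time main effect is the change that all arms share, including anything gained by repeating the task. The group main effect averages over all visits, so it mixes chance baseline differences with post-randomisation differences. The follow-up rule accepts either one as a licence for simple effects and pairwise tests.

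Three consequences follow from the literal text:

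1. A null primary interaction does not stop arm comparisons on flicking capacity.
2. A secondary outcome whose interaction fails FDR adjustment can still be opened by an unadjusted main effect.
3. Simple effects include change within each arm. Under a shared practice gain, some arms can appear to improve and others not, with no difference between arms. In a trial meant to compare HIIT with MICT, that pattern is easily misread.

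Separately, the interaction covers weeks 12 and 16 together (4 df if time is categorical). It can be significant because of week 16 alone, which is not the question in objective 1.

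**Working it through.** **Inputs from the protocol.** Three arms, 1:1:1; 52 per arm needed and 65 recruited (52 / (1 − 0.20) = 65; 65 × 3 = 195); d = 0.4; two-sided 0.05; three visits. The protocol states no error rate for the follow-up rule, so there is no figure of its own to reproduce.

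**Assumptions, not in the protocol.** Unit SD, within-person correlation ρ = 0.5 or 0.7, complete data, identity link, main effects averaged over the other factor, and a practice gain g (in SD) equal in all arms and at both later visits.

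**Step 1: how often does the time main effect open the gate?** Changes from baseline have variance 2(1 − ρ) and covariance (1 − ρ). With n per arm, the 2-df time test has noncentrality λ = 2ng²/(1 − ρ).

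- Smallest case at g = 0.1 (n = 52, ρ = 0.5): 2 × 52 × 0.01 / 0.5 = 2.08, so 23% significant.
- Largest case at g = 0.1 (n = 65, ρ = 0.7): 2 × 65 × 0.01 / 0.3 = 4.33, so 45%.

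Simulation with sandwich Wald tests (6,000 runs per setting, no arm effect) agrees:

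| Common gain | Time effect significant |
|---|---|
| 0 | about 5% |
| 0.1 SD | 24–44% |
| 0.2 SD | 75–97% |
| 0.3 SD | 98% to over 99.9% |
| 0.5 SD | 100% |

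The interaction is significant in about 5.5–6.5% of runs throughout, slightly above nominal because of the sandwich test. The whole gate (time, group or interaction) opens in about 16% of runs with no gain and in 98–100% from 0.3 SD.

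**Step 2: at least one false arm difference, gain 0.3–0.5 SD.**

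| Bonferroni family | Gate as written | Interaction-only gate |
|---|---|---|
| 3 pairs, week 12 only | 4.5–5.3% | about 0.5–1% |
| 3 pairs separately at weeks 12 and 16 | 7.7–9.4% | 1–2.5% (this row and the next) |
| 3 pairs separately at all three visits | 10.6–12.6% | as above |
| All 6 or all 9 pairs together | 4.0–4.9% | no higher than per visit |

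A second, independent set of 4,000 runs per setting gave the same picture: 4.2–5.4% for the all-pairs families and 10.3–12.9% for three separate visits.

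**Step 3: within-arm tests.** At a 0.3 SD gain, 49–70% of runs show some but not all arms as significantly improved at week 12 while the interaction is not significant. At 0.5 SD this mixed pattern is less common (about 1–27% in the second set of runs), because all three arms usually improve.

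**Step 4: the unnamed visit.** Suppose both exercise arms differ from control by 0.4 at week 12 and by w at week 16, with n = 52. Then:

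- 4-df interaction: λ = (2n/3)(0.16 − 0.4w + w²) / [1.5(1 − ρ)]
- 2-df week-12 contrast of change: λ = (2n/3)(0.16) / [2(1 − ρ)]

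Here 2n/3 = 34.67.

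| ρ | Effect at week 16 | 4-df λ, power | 2-df λ, power |
|---|---|---|---|
| 0.5 | half kept (w = 0.2) | 5.55, 44% | 5.55, 55% |
| 0.5 | all kept or all lost | 7.40, 57% | 5.55, 55% |
| 0.7 | half kept | 9.24, 68% | 9.24, 78% |
| 0.7 | all kept or all lost | 12.33, 81% | 9.24, 78% |

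Simulated values are close. The largest gap in favour of the 4-df test was 83.1% against 78.5% (ρ = 0.7, effect lost). The 4-df λ is symmetric in the two visits. An effect of 0.4 at week 16 only, with nothing at week 12, therefore also gives λ = 7.40 and a significant interaction 57% of the time (ρ = 0.5).

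**The case against.** **The practice gain is unknown.** A reader might infer that a time effect is close to certain because participants repeat an unfamiliar task. The documents do not support that. They call learning effects potential, exclude regular Aim Lab users, provide a warm-up and give no size. At 0.1 SD the time effect is significant in under half of trials. The remark about practice "leading to an increase in proficiency and potentially affecting the final game performance test" is no evidence either: it concerns loyal players of a mainstream game and explains why such a game was not used. This stands, and the size must be given as a range.

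**The primary test keeps its level, and follow-ups are adjusted.** A reader might infer that the rule inflates error in every case. It does not. The interaction is still tested at 0.05, the later tests are labelled post-hoc, and if Bonferroni spans all visits or week 12 only, false arm differences stay at about 5% or less. The excess arises only with separate application per visit, and the text does not say which is meant. What remains is that a null primary test does not stop the comparisons.

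**The rule can be read respectively.** An interaction would lead to simple effects, and a main effect only to comparisons of that factor's levels. This is ordinary practice, but the sentence does not say it. On that reading, a group main effect would still open arm comparisons that average in baseline.

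**Week 12 is implied by the objectives.** True. The analysis text does not carry it over, and it puts both visits into the test of the main hypothesis.

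**Within-arm gains are not promised as findings.** Also true; the protocol nowhere says that they will be reported as exercise effects.

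**Conclusion.** The point holds as a defect in a stated rule, not as missing detail. As written, main effects that do not isolate the randomised comparison can open arm and within-arm tests after a null primary interaction or after a secondary interaction that fails FDR adjustment. Under the assumptions above, the gate is open in about 98–100% of null trials once the shared gain reaches 0.3 SD, and much less often for a small gain. False arm differences run at about 8–13% with Bonferroni per visit and at or below about 5% otherwise.

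The second part also holds: an interaction over both visits need not mean an effect at week 12, although the objectives treat week 16 as a separate question. A reader might think that power is the reason to prefer a week-12 test. It is not: the 4-df test does as well or slightly better when the effect is fully kept or fully lost. The reason is that objective 1 asks about the 12-week effect.

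**What to change.** 1. Delete *main or* from the follow-up rule. Between-arm post-hoc tests then follow only a significant interaction (after FDR adjustment for secondary outcomes) or a contrast named in advance.
2. Name the between-arm contrast of change in flicking capacity from baseline to week 12 as primary, and the week-16 contrast as secondary. The three week-12 pairs could also be named and tested directly: with Bonferroni over three, the simulated error is about 4.5–5% without any gate.
3. State the Bonferroni family.
4. Report within-arm changes descriptively, with no claim of effect.

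The cost is wording only; conduct and sample size do not change. Against the 4-df test, the 2-df week-12 test gives up as much as about 5 points of power if the effect is fully kept or fully lost at week 16, and gains about 10 points if half is retained.
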